## **SECTION 3: TRIAL METHODS**

### **8. Trial design**

This study is a cluster-randomized controlled trial designed to test the efficacy of Preventure personality-targeted interventions on substance use, cognitive and mental health outcomes in selected, high-risk adolescents attending school in the greater Montreal Area (Quebec, Canada).

## 9. Randomisation

A dynamic allocation (DA) method will be used to allocate schools to intervention or control arms to balance baseline prognostic factors at the cluster (school) level. The Data Coordinating Centre statistician at Hôpital Sainte-Justine ([name], PI) generates randomization lists for school. The randomization process consists of computer-generated random lists of intervention allocations to school according to the Pocock–Simon modified minimization method to ensure balance across two covariates, the language of school (French, English) and the gender with three categories describing the proportion of boys in the school (< 25% boys, 25-75% boys, ≥ 75% boys). Details of the randomisation method are held securely at the Data Coordinating center (ACRU).

## 10. Sample size calculation for the primary outcome

Sample size calculations are conducted according to the sample needed for the primary long-term analyses, namely the onset of substance use disorders 4-years post-intervention in the sub-group of students identified at high-risk in grade 7. As the school (cluster) is the unit of randomisation, the sample size determination accounts for the clustering of students within schools. According to data from a local epidemiologic study and a previous personality-targeted intervention trial, the expected proportion of students with a substance use disorder in grade 11 in the control group is 10%. The minimum detectable reduction is set to 50% (i.e., 10% substance use disorders in grade 11 in the control group versus 5% in the intervention group). Assuming that this proportion per school is approximately normally distributed (i.e., 95% of the schools would fall within two standard deviations of the mean, 10%, 7 %), we obtain a between-cluster coefficient of variation,  $k$ , of 0.35. In addition, we expect 50 students per school (40-45% of the full sample) to be identified as high-risk (average cluster size of 50), following previous personality-targeted intervention studies. With these assumptions (using formula 7.7,), the number of schools (clusters) per arm needed to detect a 50% reduction in the proportion of drinkers (i.e., from 10% to 5%) with 80% power and a false positive error rate of 2.5% is 15, giving a total of 30 schools or approximately 1500 high-risk students. We plan to recruit two additional schools ( $30 + 2 = 32$  schools total) to account for potential attrition at the school-level.

For the secondary outcomes (other measures of substance use, mental health and cognition), we will use the observed effect sizes from the IMAGEN study on 2000 14 year-old European participants who completed neuropsychological assessments. Binge drinkers showed reduced IQ and a greater reward bias on the Passive Avoidance Learning Paradigm^45 relative to non-bingers where observed effect sizes ( $d$ ) for these mean differences ranged

from 0.23-0.25. Larger mean differences are expected in our study since our follow-up is longer. We also expect more cognitive development to take place in intervention participants as we expect reductions in substance use following the intervention to promote their cognitive development. Thus, we expect differences in cognitive development to increase over time between intervention and control groups. A sample size of 15 clusters per group with an average of 50 high-risk adolescents per cluster will achieve at least 90% power to detect a difference of at least 3.0 between the group means of cognitive functioning with a standard deviation of 15.0 (an effect size of 0.20)  and an intra-cluster correlation of 0.40 using a false positive error rate of 2.5%.

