### *2.11 What is the proposed sample size and what is the justification?*

Primary Analyses: Drinking outcomes at 12 and 24 months are considered established intermediate factors in the

[name]. A cluster-randomised trial investigating the effects of selective intervention on adolescent cognitive development and addiction. Amount requested 1st year: \$242,556

Research Proposal

causal pathway to substance use disorders. Primary outcomes of the current trial will focus on onset of substance use disorder at the 3 and 4-year follow-up (Grade 10 and 11), in the HR sample. Intercluster correlations were high for drinking (0.23-.27), but low for problem drinking (0.09) according to the Adventure Trial (Appendix E). Power analyses were conducted according to Donner and Klar [108, 109]. According to the tables in Appendix F, the expected proportion of students demonstrating substance use disorder in grade 10 and 11 in the control group is 10% (but should be higher in the high risk sample). According to the two-year Adventure outcomes, we expect a 50% reduction from 20% to 10%, or conservatively from 10% to 5%. As well, we are expecting this proportion to vary between schools from 3% to 17%. Further assuming that the school proportions are approximately normally distributed where 95% of the schools would fall within two standard deviations of the mean (10% +- 7%), this leads to a coefficient of variation,  $k$ , of 0.35. With these assumptions and using formula 7.7 of White [110] one can obtain the number of schools (clusters) per group needed to detect a 50% reduction in the proportion (i.e. from 10% to 5%) with 80% power and a false positive error rate of 2.5%; 15 schools per group are needed for a total of 30 schools. Two additional schools will be recruited to allow for drop-out.

Secondary Objective and Cognitive Outcomes: According to analyses on the IMAGEN sample of 2000 European 14-year olds assessed on substance use and neuropsychological measures, binge drinkers showed reduced IQ and

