### *2.14 What is the likely rate of loss to follow up? On what evidence is the loss to follow-up rate based?*

This trial protocol is much based on that of the Adventure Trial, which achieved an average follow-up rate across two treatment conditions and four follow-up periods of 84% (including the 2 schools unable to complete follow-

[name]. A cluster-randomised trial investigating the effects of selective intervention on adolescent cognitive development and addiction. Amount requested 1st year: \$242,556 Research Proposal up), with follow-up at the end of a two-year trial at 80%. We expect better follow-up in this trial, due to the less transient nature of a Montreal sample relative to a London sample, because participants will be recruited earlier in their academic career and required by law to be enrolled in school until the age of 16 years. Participation by school boards, rather than individual schools in London, will allow us to track students who transfer across schools while remaining in the trial. See Appendix D for recruitment and follow-up rates of the Adventure Trial[29].

*2.15 How many centers will be involved?* All recruitment will be conducted by CHU Ste Justine, U of Montreal, but University of Toronto and McGill will assist with data collection, management and analysis.

*2.16 What is the proposed type of analyses?*

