**15. Confidence intervals and p-values**

All applicable statistical tests will be two-sided and at the 5% significance level, unless otherwise specified, with two-sided 95% confidence intervals presented whenever possible.

**16. Description of any planned adjustments for multiplicity, and if so, including how the type 1 error is to be controlled**

As there is a single primary endpoint, and the secondary endpoints are to be used only in providing additional supportive exploratory information, and no interim analysis on the primary outcome were done, there will be no adjustments for multiple testing.

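### The 80% power for the primary outcome rests on an unsourced between-school variation (k = 0.35) that is not reconciled with the protocol's cited ICC of 0.09, and on no loss of students

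*Combined protocol and SAP*

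**What the plan says.** SAP section 10 sets the target as "10% substance use disorders in grade 11 in the control group versus 5% in the intervention group" and concludes that the number of schools needed per arm "with 80% power and a false positive error rate of 2.5% is 15, giving a total of 30 schools". Two further schools are added, for loss of whole schools only. SAP section 15 states that "All applicable statistical tests will be two-sided and at the 5% significance level", so the 2.5% error rate in section 10 is read as 2.5% per side.

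Clustering enters as a coefficient of variation. Protocol 2.11 says "we are expecting this proportion to vary between schools from 3% to 17" per cent. Treating that range as the mean plus or minus two standard deviations gives k = 0.35, and SAP section 10 repeats the step ("we obtain a between-cluster coefficient of variation"). Neither document gives a source for the range.

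The same protocol paragraph reports that "Intercluster correlations were high for drinking (0.23-.27), but low for problem drinking (0.09) according to the Adventure Trial". The 0.09 does not enter the calculation, and SAP section 10 does not mention it.

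On student follow-up, protocol 2.14 reports 84% on average for the Adventure Trial, "with follow-up at the end of a two-year trial at 80" per cent, and expects better here without giving a figure. SAP section 27.a speaks of a large amount of missing data for the binary primary outcome at 48 months.

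**The concern.** The stated power depends on two inputs that the documents do not support. The first is k. At 10% prevalence, k = 0.35 is an ICC between six and seven times smaller than the 0.09 that the protocol takes from its reference trial for a related outcome. The protocol relies on that trial for the 50% reduction but not for clustering, and does not say why. The second is complete observation of 50 high-risk students per school at four years.

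The stake is interpretation. Readers will set a null or imprecise primary result against an 80% chance of detecting a halving. If the true chance was nearer two in three, or lower, that reading would be too confident.

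**Working it through.** **Inputs.** p0 = 0.10, p1 = 0.05, k = 0.35, m = 50 and c = 15 schools per arm (SAP 10); two-sided 5% (SAP 15); ICC 0.09, scale not stated (protocol 2.11); 80% student follow-up, so m = 40 (protocol 2.14); realised high-risk numbers per intervention school (SAP 18.a, Table 2).

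**Formula.** The standard coefficient-of-variation formula for cluster-randomised proportions:

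- V = p0(1−p0)/m + p1(1−p1)/m + k²(p0² + p1²)
- c = 1 + (1.96 + 0.8416)² × V / (p0−p1)²
- power = Φ( √[(c−1)(p0−p1)²/V] − 1.96 )

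**Reproducing the plan.** V = 0.00180 + 0.00095 + 0.1225 × 0.0125 = 0.00428. c = 1 + 7.849 × 0.00428/0.0025 = 14.44, rounded up to 15. Power at 15 per arm is Φ(2.859 − 1.96) = 81.6%. The figure reproduces. Reading 2.5% as two-sided would give 17.28, so 18 per arm, which is not what the plan states.

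**Putting k and the ICC on one scale**, with ICC = k² p/(1−p):

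- k = 0.35 at p = 0.10: ICC = 0.1225 × 0.1/0.9 = 0.0136.
- ICC 0.09 on the proportion scale: k = √(0.09 × 0.9/0.1) = 0.90.
- ICC 0.09 on the logit (latent) scale: school variance = (0.09/0.91) × 3.29 = 0.325, SD 0.57. At a mean of 10%, the SD of school proportions is 0.052, so k is about 0.52 (proportion-scale ICC about 0.030).

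**Power at 10% v 5%, two-sided 5%:**

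| k | m | V | 15 per arm | 16 per arm | schools per arm for 80% |
|---|---|---|---|---|---|
| 0.35 | 50 | 0.00428 | 81.6% | 84.1% | 15 |
| 0.35 | 40 | 0.00497 | 75.6% | 78.4% | 17 |
| 0.52 | 50 | 0.00614 | 66.5% | 69.5% | 21 |
| 0.52 | 40 | 0.00683 | 61.9% | 64.9% | 23 |
| 0.90 | 50 | 0.01288 | 37.8% | 40.0% | 42 |
| 0.90 | 40 | 0.01356 | 36.2% | 38.3% | 44 |

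At m = 50, 80% power requires k no higher than 0.37 with 15 per arm, or 0.40 with 16. At m = 40 the limits are 0.29 and 0.33.

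**Unequal school sizes.** Table 2 lists 709 high-risk students in 15 schools: mean 47.3, range 14 to 86, coefficient of variation 0.40. Apply these sizes to both arms, keep 80% of students and k = 0.35, and weight each school by its precision. Each arm's variance is then 1/Σ[1/(p(1−p)/(0.8mᵢ) + k²p²)]. The two arms sum to 0.000356. Multiplying by 15 gives V = 0.00534, and power is Φ(2.560 − 1.96), about 73% with 15 per arm.

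**The 20% v 10% case.** The protocol also writes "we expect a 50% reduction from 20% to 10%, or conservatively from 10% to 5" per cent. At 20% v 10% with 15 per arm:

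- k = 0.35: 94% (m = 50) or 92% (m = 40).
- Logit reading (k about 0.44): 87% or 84%.
- Proportion reading (k = √(0.09 × 0.8/0.2) = 0.60): 69% or 67%.

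**The case against.** The strongest reply is that 0.09 does not belong to this endpoint. It describes problem drinking in a London trial with two years of follow-up. The outcome here is a DEP-ADO total score covering alcohol and drugs, at four years, in Montreal. The text available does not give its scale, and it may be unadjusted: protocol 2.16 says that unconditional models produced the between-school variances for drinking. The planned analysis adjusts for school language, gender mix and immigration status (SAP 26.b, adjustments), which may reduce residual clustering by an amount that the documents do not give. All of this stands. It is why 0.09 gives a range and cannot simply replace k. It does not supply a source for 0.35.

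On student loss, the protocol expects better follow-up than the earlier trial, and the SAP imputes missing outcomes, which may recover some information. That also stands. By itself, 20% loss costs about 6 points.

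The protocol calls 10% v 5% conservative and expects a higher rate in high-risk students. At 20% v 10%, power exceeds 80% except on the proportion reading of 0.09. But SAP section 10 makes its claim at 10% v 5% and does not carry the 20% case.

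A reader might go further in three ways that the documents do not support:

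- That the sample size is miscalculated. It is correct on its inputs.
- That a true halving would more likely be missed than found. This holds only on the proportion reading; on the logit reading, power is 62% to 67%.
- That Table 2 sizes with 20% loss reduce power to 67% at k = 0.35. That figure uses the harmonic mean school size (37.9 × 0.8 = 30.3), which suits an unweighted comparison of school proportions. The primary analysis in SAP 26.a is a student-level two-level model, for which about 73% is the closer figure.

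**Conclusion.** The concern holds as an unsupported and unreconciled input, not as an arithmetic error or a proven contradiction. At the SAP's own 10% v 5%, power falls below 80% on either reading of 0.09 and also with 20% student loss alone, even if all 16 schools per arm stay (78%). There is almost no margin: with 15 per arm and every student observed, k may rise only from 0.35 to 0.37.

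The size of the shortfall is conditional. It rests on three assumptions: that 0.09 carries over to a positive DEP-ADO screen in this trial, that 80% follow-up carries over from two years to four, and which scale 0.09 is on. The documents settle none of these. They support replacing an unqualified 80% with a range. They do not support a claim that the trial was in fact underpowered.

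**What to change.** In SAP section 10:

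- Replace the single power figure with a table over k (0.35, about 0.52 and 0.90) and student follow-up (m = 50 and m = 40), at 10% v 5%. The 20% v 10% case can stand beside it, labelled as the less conservative one.
- Give the basis for the 3% to 17% school range, state the scale of the 0.09, and say why k = 0.35 was preferred to the value that 0.09 implies.
- State that the two added schools cover loss of schools only.

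In the report, give the observed ICC or k with its interval beside the primary result, so that readers can see where in the range the trial fell.

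The cost is wording and one extra reported quantity. The stated power becomes less favourable. No extra schools are needed, and the primary analysis does not change.

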## **11. Framework**

The objective of the trial is to test the superiority of the intervention from control on primary and secondary outcomes.

## **12. Statistical interim analyses and stopping guidance**

Interim analyses at 12 and 24-month follow up will be conducted to confirm that the trial has had expected effects on drinking and illicit drug use behaviour and to check that there are no harmful effects of the intervention. These findings will be conducted by the data management committee and reported to the independent data monitoring committee who will keep results confidential unless harmful effects are indicated and recommendations for trial termination are made. Cognitive and addiction outcomes will be analysed at the end of the trial.

The executive and data monitoring committee decided that interim analyses would not be conducted to reduce any potential bias of introduced by interim findings on primary outcomes. As there wasn't any concern associated with potential harm from the intervention, in association with previous trials, there was no justification for introducing this potential bias to the study design.

## **13. Timing of final analysis**

The final analysis of the intervention is conducted when all students have completed outcomes assessment at 48-months follow-up (post intervention).

## **14. Visit map: Outcomes and main interest variables collection time points**

Outcomes and timing are presented in Visit Map Table 1 in details. Table 1 presents the outcomes and other variable that were collected at different time points. The length between follow-ups in each school is 12-month.

Table 1. Schedule of enrolment, interventions, and assessments of the study in schools.

|                                |                                                       | Pre-Intervention | Intervention period | Post-Intervention
Number of months after the initiation of the intervention |          |          |          |               |
|--------------------------------|-------------------------------------------------------|------------------|---------------------|--------------------------------------------------------------------------------|----------|----------|----------|---------------|
| Categories                     | Variables                                             | Baseline         |                     | 12-month                                                                       | 24-month | 36-month | 48-month | Variable type |
| Primary outcomes        | Substance use disorder                                | •                |                     | •                                                                              | •        | •        | •        | Continuous    |
| Secondary substance use | Non-verbal functioning and abstract reasoning         | •                |                     | •                                                                              | •        | •        | •        | Continuous    |
|                                | Verbal and visual memory                              | •                |                     | •                                                                              | •        | •        | •        | Continuous    |
|                                | Cognitive control and response inhibition             | •                |                     | •                                                                              | •        | •        | •        | Continuous    |
|                                | Spatial working memory                                | •                |                     | •                                                                              | •        | •        | •        | Continuous    |
|                                | Mental health symptoms                                | •                |                     | •                                                                              | •        | •        | •        | Continuous    |
|                                | Onset, Frequency and quantity of alcohol and drug use | •                |                     | •                                                                              | •        | •        | •        | Continuous    |
| Demographics            | Sex                                                   | •                |                     | •                                                                              | •        | •        | •        | Binary        |
|                                | Socioeconomic status                                  | •                |                     | •                                                                              | •        | •        | •        | Continuous    |
|                                | Immigrant background                                  | •                |                     | •                                                                              | •        | •        | •        | Categorical   |

Abbreviation:

\*: Measured at school level.

**15. Confidence intervals and p-values**

All applicable statistical tests will be two-sided and at the 5% significance level, unless otherwise specified, with two-sided 95% confidence intervals presented whenever possible.

**16. Description of any planned adjustments for multiplicity, and if so, including how the type 1 error is to be controlled**

As there is a single primary endpoint, and the secondary endpoints are to be used only in providing additional supportive exploratory information, and no interim analysis on the primary outcome were done, there will be no adjustments for multiple testing.

**18. Compliance/or adherence and protocols deviations****18.a How adherence to the intervention will be presented**

Compliance will be defined as being able to conduct all five assessments and, for intervention schools, being able to provide interventions to 85% of all high-risk youth in their school. Based on previous studies, schools generally had little difficulty complying and implementing the protocol, with only one school dropping out of the Adventure Trial due to systematic problems within the school and an impending school closure. Another intervention school was unable to complete the protocol for running sufficient interventions sessions with HR students and was thus not included in the trial. However, the main objective of the Adventure Trial was to evaluate effectiveness of the Programme, so research staff in this previous study could not offer additional support to schools if they could not deliver a certain aspect of the intervention protocol. Effectiveness will not be evaluated in the proposed study, and the current protocol will allow research staff to assist schools in meeting demands of the research or intervention protocol, thus further improving compliance rates in the proposed trial. Based on recruitment rates from the three previous trials, student participation rates are anticipated as being >85%, and with a passive parental consent procedure, we should see very little attrition due to non-consent. One of the main sources of attrition in school-based research is requiring that parents provide active, signed consent for their child to participate. Passive consent was used at various stages in the three previous trials conducted by the PI and are easily justified to an ethics committee by our data suggesting that high risk youth are more likely to volunteer to participate in these preventative interventions, but less likely to be able to provide signed consent forms from their parents, likely due to personality and related cognitive difficulties in the child or the family.

The following table provides an estimate of degree of compliance. As does school-level follow-up rate at each year (see CONSORT Figure 2).

Table 2: Participation of high-risk youth in intervention sessions and format of intervention delivery by school.

| Intervention school | Intervention Delivery      | High risk students | Students completed at least one intervention session | Students completed both intervention sessions |
|----------------------------|-----------------------------------|---------------------------|-------------------------------------------------------------|------------------------------------------------------|
| 1                          | School staff                      | 38                        | 23 (61%)                                                    | 21 (55%)                                             |
| 2                          | Research Therapists               | 56                        | 56 (100%)                                                   | 55 (98%)                                             |
| 3                          | School Staff                      | 54                        | 54 (100%)                                                   | 51 (94%)                                             |
| 4                          | Research Therapists               | 63                        | 60 (95%)                                                    | 44 (70%)                                             |
| 5                          | Research Therapists               | 56                        | 35 (63%)                                                    | 30 (54%)                                             |
| 6                          | School Staff                      | 51                        | 51 (100%)                                                   | 51 (100%)                                            |
| 7                          | School Staff + Research Therapist | 66                        | 65 (98%)                                                    | 59 (89%)                                             |
| 8                          | Research Therapists               | 52                        | 49 (94%)                                                    | 47 (90%)                                             |
| 9                          | School Staff + Research Therapist | 57                        | 29 (51%)                                                    | 29 (51%)                                             |
| 10                         | School Staff + Research Therapist | 86                        | 68 (79%)                                                    | 60 (70%)                                             |
| 11                         | School Staff                      | 14                        | 14 (100%)                                                   | 13 (93%)                                             |
| 12                         | School Staff                      | 21                        | 17 (81%)                                                    | 17 (81%)                                             |
| 13                         | School Staff                      | 34                        | 32 (94%)                                                    | 31 (91%)                                             |
| 14                         | School Staff + Research Therapist | 36                        | 35 (97%)                                                    | 28 (78%)                                             |
| 15                         | Research Therapist                | 25                        | 25 (100%)                                                   | 25 (100%)                                            |
|                            |                                   | Total: 709                | Mean: 86%                                                   | Mean: 79%                                            |

Training in intervention delivery will be offered to up to five staff-members per intervention school (e.g., school counsellors and special educational needs staff). Facilitators will attend a 3-day workshop reviewing the necessary therapeutic principles involving didactic instruction and role-play. Trainees will receive a minimum of 4 hours of supervision and feedback from the clinical team in conducting a full intervention with grade 8-10 students (not involved in the trial). High-risk youth in intervention schools will receive interventions from a trained school-based facilitator and co-facilitator. If schools do not have the resources to run all the intervention groups themselves, trained members of the clinical research team (master's

level therapists and a clinical psychology PhD student) will deliver some or all of the interventions (see Table 1 for details).

Fidelity and adherence were assessed on a random 30% of all intervention sessions, using the Preventure Intervention Fidelity and Adherence (PIFA). This scale was used developed by the principal investigator (PC) to evaluate adherence to 12 core treatment components of the Preventure program (e.g., goal setting, identifying and challenging automatic thoughts). The scale also measures fidelity by rating quality of intervention delivery (see next section).

